## Methods/Design

### Study design

This is a multicenter, randomized, double-blinded, sham-controlled, parallel-group trial in a 1:1 allocation ratio. Potential subjects will be screened from among patients attending urology or obstetrics and gynecology clinics of the participating hospitals in Northern Malaysia: Island Hospital, Lam Wah Ee Hospital, Penang Adventist Hospital, Pantai Hospital, Metro Specialist Hospital and Loh Guan Lye Hospital, as well as from among the general population through advertisements in posters, brochures, newspapers and websites. The diagnosis of UI will be made by either the urologist or the gynecologist [1]. Methods, definitions and units conform to the standards jointly recommended by the International Continence Society and the International Urogynecological Association, except where specifically noted [1]. The flowchart and study design schedule are presented in Fig. 1 and Table 1, respectively.

**Fig. 1 Fig1:**
[figure not shown]
Trial flowchart

**Table 1 Tab1:** Study design schedule

	Screening and baseline	Treatments					Follow–up		
Visit	0	1	2–7	8	9–15	16	17	18	19
Timeline (wk)	0	1	1–4	4	5–8	8	12	20	32
Screening for eligibility	x								
Informed consent	x								
Demographic data and medical history	x								
Physical examination	x								
Urine analysis	x								
Random blood sugar	x								
UPT	x					x			
Uroflowmetry with postvoid residual (ultrasound)	x					x			
Randomization		x							
MS treatment		x	x	x	x	x			
Adverse events		x	x	x	x	x	x	x	x
Retreatment or new intervention							x	x	x
ICIQ-UI-SF	x			x		x	x	x	x
Incontinence episode diary	x			x		x	x	x	x
1-hr pad test	x			x		x	x	x	x
PFMF (perineometer)	x			x		x	x	x	x
PGI-I				x		x	x	x	x
ICIQ-LUTS-QoL	x			x		x	x	x	x
EQ-5D	x			x		x	x	x	x
Blinding assessment						x			

*Abbreviations: ICIQ-LUTS-QoL* International Consultation on Incontinence Questionnaire–Lower Urinary Tract Symptoms Quality of Life, *ICIQ-UI-SF* International Consultation on Incontinence Questionnaire for Urinary Incontinence Short Form, *MS* magnetic stimulation, *PFMF* pelvic floor muscle function, *PGI-I* Patient Global Impression of Improvement, *UPT* urine pregnancy test

### Study population

#### Inclusion criteria

To be eligible for participation, subjects are required to fulfill the following conditions: (1) female aged 21 years and older, (2) demonstration of urine leak on coughing at a bladder volume of approximately 200 to 250 ml, (3) International Consultation on Incontinence Questionnaire for Urinary Incontinence Short Form (ICIQ-UI-SF) score of at least 6 points (range: 0–21), (4) must be able and agree to carry out 1-hour pad test and (5) voluntary participation and signing of the informed consent form. Urodynamic testing will not be performed as an eligibility criterion [21].

#### Exclusion criteria

The following are the exclusion criteria: (1) patients with urgency UI, mixed UI or overflow UI; (2) acute severe infections (e.g., pneumonia); (3) severe cardiac arrhythmia; (4) cardiac pacemaker or other implanted metallic devices; (5) neurologic conditions (e.g., stroke, epilepsy, Parkinson disease, multiple sclerosis); (6) random blood sugar above 10 mmol/L; (7) pregnant or actively trying to conceive; (8) previous surgery for SUI; (9) pelvic or gynecological surgery for less than 3 weeks or in the next 8 weeks; (10) previous treatment with MS; (11) history of pelvic irradiation; (12) concurrent medications with α-adrenergic antagonists (e.g., terazosin, tamsulosin, doxazosin), diuretics, serotonin-norepinephrine reuptake inhibitors or any other medications known to worsen incontinence; (13) stage III or IV pelvic organ prolapse according to Pelvic Organ Prolapse Quantification System [22]; (14) severe urethral sphincter weakness and/or defect; (15) suspected urethral and/or vesical fistula; (16) urinary tract infection or hematuria; and/or (17) postvoid residual volume greater than 200 ml.

#### Additional restrictions

Subjects of childbearing age who are not actively conceiving are required to be on any effective contraception methods, including (1) established use of oral, injected or implanted hormonal methods of contraception; (2) placement of an intrauterine device or intrauterine system; (3) barrier methods of contraception, including condom or occlusive cap (diaphragm or cervical or vault caps) with spermicidal foam, gel, film, cream or suppository; (4) male sterilization (with the appropriate postvasectomy documentation of the absence of sperm in the ejaculate); and (5) true abstinence.

Subjects who are taking α-adrenergic antagonists or any other medications known to worsen incontinence will be recruited into the study only if the medications can be discontinued. If the medications can be discontinued, the subjects will undergo a 14-day washout period and then be reassessed for eligibility.

Subjects are prohibited from starting additional specific treatments for SUI, including PFMT, biofeedback, vaginal cone, electrical stimulation or pharmacological treatments such as duloxetine.

### Interventions

All subjects will be provided with counseling on lifestyle modification, including (1) appropriate fluid consumption (between 2 and 2.5 L/24 hr or approximately 250 ml/2 hr), (2) weight reduction if body mass index is 30 or higher and (3) caffeine reduction (limited to one to two cups per day).

The intervention will involve the use of QRS-1010 PelviCenter (QRS International, Ruggell, Liechtenstein) (Fig. 2). This medical device uses electromagnetic pulsing technology for pelvic floor muscle stimulation, which was approved as a conservative treatment for UI by the U.S. Food and Drug Administration in June 1998 [11] and by the European Commission in January 2011. It generates a homogeneous magnetic field via a magnetic coil embedded beneath the surface of the seat. When applied with high electric currents, the magnetic coil generates pulsed electromagnetic fields that are able to penetrate deep into the pelvic floor to reach the relevant conductive tissues. The changing magnetic field induces a flow of ions to propagate electrical eddy currents. A voltage gradient ensues, and membrane depolarization occurs. During this consistent trajectory, a sufficiently large membrane depolarization will result in an action potential along the nerve tissues. In the pelvic floor, this leads to pelvic floor nerve stimulation (stimulation of motor end plates) and ultimately pelvic floor muscle contraction [11, 23].

**Fig. 2 Fig2:**
[figure not shown]
QRS-1010 PelviCenter magnetic stimulation device

In both groups, treatment involves two sessions of 20 minutes each per week for 8 weeks (16 sessions total). After the 8-week treatment, subjects who are not satisfied with their treatment outcome will be given the opportunity to enroll in an open-label phase, regardless of their treatment allocation. Subjects will be considered treatment defaulters if they miss treatments for more than 2 consecutive weeks.

#### Active magnetic stimulation

Subjects will be seated with the perineum in the middle of the seat to allow for the greatest effect of the pulsing magnetic field on the pelvic floor and sphincter muscles. Stimulation intensity will be gradually increased, beginning with 20 % simulation on the first session, followed by increments of 20 % (or maximum tolerable stimulation) until they receive stimuli at 100 % intensity using a stimulation repetition cycle of 50 Hz in an 8-s “on” 4-s “off” pulsing manner by a study nurse not involved in the assessments.

#### Sham magnetic stimulation

To ensure that sham subjects’ experiences are similar to the intervention, the sham group will undergo the same number, duration and frequency of treatments as the active group using the same MS device and stimulation frequency. However, unlike the intervention, the magnetic coil will be tilted to 22° down with a lower stimulation intensity, beginning with 20 % simulation intensity at the first session, followed by gradually increasing increments of 20 % intensity after every five sessions until a maximum of 60 % intensity is reached (Fig. 3). The combination of these methods has been shown to provide a total energy output of 136 kJ, (or 8.500 J each session) during the 8-week study period, which is far less than the energy output of one 20-minute active mode run (at 100 % intensity) of 408 kJ, thus providing a similar appearance as the active treatment.

**Fig. 3 Fig3:**
[figure not shown]
Flux generator positions of active versus sham stimulation

### Study outcomes

#### Primary outcome

The primary outcome measure is the improvement in the severity of involuntary urine loss. This is measured by the self-administered ICIQ-UI-SF, which measures frequency, volume and impact on daily life of involuntary urine loss. The ICIQ-UI-SF has undergone extensive psychometric testing and is graded A (highly recommended by the International Consultation of Incontinence) as an outcome measure in research trials [24]. The primary criterion for response is defined as having a 5-point or greater reduction in the ICIQ-UI-SF score (score range: 0–21) from baseline to 8 weeks [25–27]. The responder criterion of at least a 5-point decrease will allow detection of clinically significant improvement in SUI symptoms.

#### Secondary outcomes

CureAs the ultimate aim of treatment is to achieve complete continence, this is measured through a combination of an objective and a subjective outcome measure. *Cure* is defined as a leakage of less than 1 g on the pad test [28] or a “never” response to question 3 of the ICIQ-UI-SF, “How often do you leak urine?”SUI-related symptomsIncontinence episode frequency (IEF)Symptoms relevant to SUI (incontinence episodes and complications) will be measured using a self-completed incontinence diary. The outcome measure is the number of responders, defined as having at least a 50 % reduction in IEF compared with baseline [29]. The average daily incontinence episode is calculated on the basis of a 3-day incontinence episode diary.1-hour pad testThe outcome measure is the number of responders, defined as having a decrease of 50 % or more in pad weight compared with baseline [14]. The 1-hour pad test will be conducted according to guidelines published by the International Continence Society [30]. However, the test will be initiated when the bladder volume is at 250 ml (as measured by abdominal ultrasound) instead of drinking 500 ml of liquid. The modification is based on recommendations from the Fifth International Consultation of Incontinence, in which experimental conditions for short-term pad tests must include a standardized bladder volume [28]. Subjects are judged as dry when leakage is less than 1 g on the pad test and as improved when pad weight decreases by 50 % or more [14, 28].Pelvic floor muscle strengthThe outcome measure will be an improvement in the pelvic floor muscle strength compared with baseline as measured using the Peritron perineometer (LABORIE International, Mississauga, ON, Canada) [31, 32]. The Peritron is a pressure-sensitive dynamometer used for objective assessment of the strength of pelvic floor muscle contractions. For each subject, a sterile latex sleeve is fitted around the silicone rubber sheath and inserted into the vagina. After restoring to point 0, the subjects will be asked to perform a maximal pelvic floor contraction. After each contraction, the calibrated 0 point will be restored. The peak, average and duration of contraction for three consecutive contractions will be measured and recorded.Incontinence severitySubjects are divided into the following four categories of SUI severity according to the ICIQ-UI-SF score: slight (1–5), moderate (6–12), severe (13–18) and very severe (19–21) [33]. The outcome measure will be the number of responders, defined as at least one level of improvement in severity groups (e.g., from moderate to mild).Quality of life (QoL)Another measure of treatment success can be defined as an improvement in the subjects’ QoL. To ensure that these measures are captured and reported, the following questionnaires will be used:Patient Global Impression of Improvement (PGI-I), a single-item generic measure that allows subjects to rate their condition regarding their response to the therapy. The outcome measure is the number of responders, defined as subjects who answer “very much better” and “much better” to the PGI-I question [34].The International Consultation on Incontinence Questionnaire–Lower Urinary Tract Symptoms Quality of Life, which is based on the King’s Health Questionnaire [35], is a condition-specific questionnaire used to evaluate the QoL of UI patients. The possible score ranges from 19 to 76, with higher values indicating increased impact on QoL. The outcome measure will be an improvement in the QoL of subjects compared with baseline [35, 36].The EQ-5D is a simple, generic QoL measure that is able to provide a single index status. This will be subsequently converted into a weighted health state index using the Malaysian value sets.

### Health economic evaluation and analysis

In addition to the evaluation of clinical treatment effectiveness, a prospective assessment of health economic issues is being planned. A cost-effectiveness analysis using patient-reported outcomes will be performed. To estimate costs, the resource use is measured in natural units (e.g., duration of treatment in minutes). The average resource use per patient is calculated and priced with opportunity cost approximated over Malaysian market prices or schedule prices (e.g., wage agreements for staff costs). A sensitivity analysis is performed by replacing the mean costs and effects with the upper and lower bounds of the respective 95 % confidence intervals. Costs and effectiveness results are synthesized in an incremental cost-effectiveness ratio.

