### Aims of the study

The aim of the study is to investigate the effects of MS in female patients with SUI. Furthermore, we intend to show that MS therapy is safe and effective when provided in a community setting and to prove its overall cost-effectiveness. The following research questions were developed:What is the efficacy of MS in female patients with SUI?Does the use of MS lead to a better QoL in patients with SUI?Is the use of MS cost-effective compared with the conventional therapy?After the first 2 months of treatment:How effective is active MS in patients who did not respond to the initial sham treatment?Does longer treatment with active MS improve treatment response in the initial active group?

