### Statistical methods

#### Sample size calculation

Two types of sample size calculations were performed: non-repeated measures and repeated measures. Our primary outcome of interest is the difference in proportion of responders between the active and sham groups after 8 weeks of treatment, defined as a reduction of 5 points or more from baseline to 8 weeks in the ICIQ-UI-SF total score. On the basis of outcomes derived from previously published data on MS, it is anticipated that MS will improve symptoms in 60 % (p1 = 0.6) of subjects with SUI, whereas sham MS will improve symptoms in 30 % (p2 = 0.3) of subjects with SUI [11, 13]. Thus, a minimum sample size of 88 (44 per arm) is powered to detect a difference of at least 30 % (δ = 0.3), with a 95 % confidence interval (α = 0.05) and statistical power of 80 % (β = 0.2) [38]. Allowing for a 25 % dropout rate, the enrollment goal is 120 subjects.

We also calculated our sample size using PASS^13^ Sample Size Software (NCSS Statistical Software, Kaysville, UT, USA) [39]. The tests for two proportions in a repeated-measures design, which can be used to calculate sample size in a mixed-model analysis of repeated measures data, was selected from among the PASS^13^ statistical tools. Using the same parameters (δ = 0.3, α = 0.05 and β = 0.2), an autoregressive AR(1) covariance pattern with autocorrelation of 1.0, and a design with six repeated measurements, a total sample size of 84 (*n* = 42 in each arm) was obtained. As the sample size calculated using a test of simple differences in proportion was higher, we selected the initial calculated sample size.

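### Substituting the separate 95 % limits of mean costs and effects does not give a 95 % range for the incremental cost-effectiveness ratio, on either reading of which limits are meant

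*Protocol article*

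**What the plan says.** Under Aims of the study, the protocol article intends "to prove its overall cost-effectiveness". The method is in Health economic evaluation and analysis:

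- Effect: "A cost-effectiveness analysis using patient-reported outcomes will be performed". The outcome is not named.
- Cost: "The average resource use per patient is calculated and priced with opportunity cost", approximated by Malaysian market or schedule prices.
- Uncertainty: "A sensitivity analysis is performed by replacing the mean costs and effects with the upper and lower bounds of the respective" 95 % confidence intervals.
- Synthesis: "Costs and effectiveness results are synthesized in an incremental cost-effectiveness ratio".

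No other method for uncertainty in the ratio is named, and the correlation between a patient's cost and her effect is not mentioned. The section does not say whether the intervals are those of each arm's mean or of the incremental cost and incremental effect. It attaches no coverage level, test or decision rule to the result.

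**The concern.** Cost-effectiveness is a statement about incremental cost and incremental effect together. Limits that each hold at 95 % for one mean do not combine into a 95 % statement about a difference, still less about a ratio of two differences. Per-arm limits make the range too wide because standard errors are added rather than combined in quadrature. Incremental limits still treat cost and effect as if any corner were as plausible as any other. A ratio also misbehaves when its denominator may be zero: it changes sign and passes through infinity, so the most extreme corners no longer enclose it. At stake is a secondary but stated aim. A reader would probably take the resulting range as the trial's error bar on the ICER, and it is not one.

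**Working it through.** **Inputs.** From Sample size calculation: "it is anticipated that MS will improve symptoms in 60 % (p1 = 0.6) of subjects with SUI", "sham MS will improve symptoms in 30 % (p2 = 0.3) of subjects with SUI", and "Thus, a minimum sample size of 88 (44 per arm) is powered to detect a difference"; also α = 0.05, power 80 %, 25 % dropout and 120 enrolled, so 60 per arm. Assumed: the economic effect is the ICIQ-UI-SF responder rate. The standard deviations of cost and the cost-effect correlation are not given, so ranges are used.

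**The article's own figure.** With a mean proportion of 0.45, n = 2 × 0.45 × 0.55 × (1.96 + 0.8416)² / 0.30² = 43.2, so 44 per arm and 88 in all. Dropout: 88 / 0.75 = 117.3, rounded up to 120. The sample size reproduces. The economic section states no figure to reproduce.

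**Reading 1: limits of each arm's mean.** The half-width of the corner range is 1.96 (SE₁ + SE₂); the proper half-width is 1.96 √(SE₁² + SE₂²).

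At 60 per arm:
- SE₁ = √(0.24/60) = 0.0632 and SE₂ = √(0.21/60) = 0.0592.
- Corner half-width: 1.96 × 0.1224 = 0.240, so 6 to 54 points. At a fixed incremental cost the ratio varies 54/6 = 9-fold.
- Proper half-width: 1.96 × 0.0866 = 0.170, so 13 to 47 points, a 3.6-fold range.
- Coverage: z = 1.96 × 0.1224 / 0.0866 = 2.77, so 2Φ(2.77) − 1 = 99.4 %. For SE ratios from 1 to 3 it lies between 99.4 % and 98.7 %.

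This is the coverage of one difference, on one axis. If cost behaves the same way and is independent of effect, the joint figure is about 0.9944² = 98.9 %.

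**Reading 2: limits of the increments.** Each axis covers 95 %. The box covers 0.95² = 90.25 % jointly if cost and effect are independent, and between 90 % and 95 % in general. Its corners are the same whatever the correlation.

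**The ratio itself.** Simulations took true incremental effects of 2.8 and 3.3 standard errors, true incremental costs of 3, 6 and 12 standard errors, and correlations of −0.5, 0 and 0.5. Where the lower effect limit was above zero, the extreme corner ratios covered the true ICER in about 98 % to 100 % of trials on both readings. So even where the box under-covers the pair, the range read off its corners is too wide for the ratio.

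**Effect limits that include zero.** Take a positive incremental cost c and effect limits L < 0 < U. The ratios compatible with those limits lie above c/U or below c/L. The stretch between the two corner values is exactly what is excluded, so the corners bound nothing. In the same simulations the lower effect limit was at or below zero in about 20 % of trials (2.8 SE) and 9 % (3.3 SE) with incremental limits, and in about 49 % and 30 % with per-arm limits.

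**The case against.** The strongest reply is that the article calls this step a sensitivity analysis. It varies inputs over a range and never presents the outcome as a 95 % interval. That stands, and it rules out two stronger readings.

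- A reader might infer that the method costs the trial power. With per-arm limits, the chance that every corner shows a positive incremental effect is about 75 % at 60 per arm, against 92 % for a proper interval. But no test is attached to the corners. The only power target concerns the clinical responder outcome, analysed by generalised linear mixed model, and it is untouched.
- A reader might take 99.4 % as joint coverage of cost and effect. It is a one-axis figure and holds only for per-arm limits, which the text does not specify.

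The magnitude also depends on an assumed effect measure. Nor is shrinking to 45 completers per arm the article's own scenario, because Statistical analysis counts withdrawals as failures and keeps them in the denominator. If 60 % and 30 % are completers' rates and 25 % drop out of each arm, the rates become 45 % and 22.5 % of 60. The corner half-width is then 1.96 × (0.0642 + 0.0539) = 0.232, giving −0.7 to 45.7 points; the proper half-width is 1.96 × 0.0839 = 0.164, giving 6.1 to 38.9. So respecting that rule does not rescue the corners.

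A full protocol or analysis plan, not shown, may add a joint method, and leaving such detail out of an article is no fault. The point here is the method that the article does state.

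Finally, the research question compares magnetic stimulation with conventional therapy, and the trial has no such arm. Better handling of uncertainty cannot supply that comparison.

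**Conclusion.** The point holds in a limited form. The one uncertainty method stated for the ICER leaves open which limits are used, ignores the cost-effect correlation, and gives no 95 % range for the ratio on either reading. Its size depends on the reading: about 99.4 % coverage on one axis with per-arm limits (6 to 54 points against 13 to 47, assuming 60 % v 30 % response and 60 per arm), or about 90 % to 95 % joint coverage of the box with incremental limits. When the effect limits include zero, the corner ratios do not bound the ICER on either reading. The consequence is confined to the economic aim; the efficacy conclusion does not depend on it.

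**What to change.** Make the main uncertainty analysis a non-parametric bootstrap that resamples patients within arm and keeps each patient's cost and effect together. Report:

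- incremental cost and incremental effect, each with a 95 % confidence interval;
- incremental net monetary benefit and an acceptability curve over a stated range of willingness-to-pay values. Net benefit stays defined when the effect limits include zero.

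If the substitution of limits is kept, label it a descriptive one-way sensitivity check, say whether the limits are per-arm or incremental, and do not present the result as a 95 % interval. State that the analysis informs active v sham only.

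The cost is a few hours of analysis on data already planned, with resource use priced for each patient rather than only on average, and a willingness-to-pay range fixed in advance. Trial status reports that follow-up was still running, so the change could be made before analysis.
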